## Abstract

**Background:**

Human papillomavirus (HPV)-based screening is increasingly being adopted as the primary strategy for cervical cancer prevention due to its superior sensitivity compared with cytology. However, effective triage of women who test positive for high-risk HPV (hrHPV), particularly those infected with non-HPV16/18 genotypes, remains a significant challenge in low-resource settings. Cytology-based triage requires substantial laboratory infrastructure and technical expertise, which may limit its scalability. Risk-stratified triage approaches incorporating readily available clinical and demographic factors may offer a practical alternative for identifying women at highest risk of cervical precancer while reducing unnecessary referrals.

**Aim:**

The “*STRAT-CIN Trial*” aims to determine whether a risk-stratified triage algorithm is non-inferior to standard cytology-based triage for the detection of high-grade cervical intraepithelial neoplasia (CIN2+) among women positive for non-HPV16/18 high-risk HPV types.

**Methods:**

This protocol describes a two-arm, parallel, open-label, non-inferiority randomized controlled trial involving sexually active women aged 30–65 years who test positive for non-HPV16/18 high-risk HPV types during routine cervical cancer screening at the Lagos University Teaching Hospital (LUTH), Lagos, Nigeria, between June 2026 and January 2027. A total of 148 eligible women will be randomized in a 1:1 ratio to either a risk-stratified triage arm or a cytology-based triage arm. Participants in the intervention arm will be triaged using a composite algorithm incorporating age, HIV status, cigarette smoking, long-term oral contraceptive use, and multiple hrHPV genotype infections, while participants in the control arm will undergo reflex cytology according to the Bethesda 2014 classification. The primary outcome is the proportion of histologically confirmed CIN2 + lesions detected in each study arm. Secondary outcomes include diagnostic performance metrics, referral rates for colposcopy, colposcopic yield, and predictors of CIN2+. Analyses will follow the intention-to-treat principle. Differences in CIN2 + detection rates will be assessed using risk differences and corresponding 95% confidence intervals. Non-inferiority will be concluded if the lower bound of the confidence interval exceeds the pre-specified non-inferiority margin of − 10%. Logistic regression analyses will be used to identify independent predictors of CIN2+, and statistical significance will be set at P < 0.05.

**Discussion:**

The “*STRAT-CIN Trial*” will evaluate whether a simplified risk-stratified triage approach can achieve diagnostic performance comparable to conventional cytology-based triage among women with non-HPV16/18 high-risk HPV infections. By integrating easily obtainable clinical and demographic risk factors into triage decision-making, this study has the potential to reduce unnecessary colposcopy referrals, improve screening efficiency, and support the implementation of context-appropriate cervical cancer prevention strategies in resource-constrained settings. The findings will contribute important evidence toward optimizing HPV-based cervical cancer screening programs in Nigeria and other low-and middle-income countries.

**Registration:**

: PACTR202606895128487 (2nd June 2026).

## Introduction

Cervical cancer remains a major public health threat worldwide, with over 80% of cases and deaths occurring in low- and middle-income countries (LMICs) [1]. Recent global burden estimates indicate that women in low Human Development Index (HDI) regions experience nearly three times the incidence and up to six times the mortality compared to those in high-HDI countries [2, 3]. In sub-Saharan Africa, cervical cancer is among the leading causes of female cancer mortality, often affecting women during their most productive years, thereby imposing substantial socioeconomic and familial burdens [4]. In Nigeria alone, approximately 15,000 new cases are diagnosed annually, with nearly two-thirds resulting in death [5].

Persistent infection with high-risk human papillomavirus (hrHPV) is the established cause of cervical cancer [6]. As a result, HPV-based screening is increasingly being adopted as the primary screening method due to its superior sensitivity relative to cytology (Pap smear) [7, 8]. However, because HPV testing detects transient infections as well as clinically significant lesions, triage strategies for hrHPV-positive women are essential to preserve specificity and reduce unnecessary referrals. A widely adopted approach combines partial HPV genotyping—identifying HPV16/18, the types most strongly associated with cervical carcinogenesis—with reflex cytology for other high-risk types [9]. The COMPACT (COMparison of HPV genotyping And Cytology Triage) trial, for instance, demonstrated that women infected with HPV16/18 had markedly higher absolute risks of CIN2 + compared to those harbouring other hrHPV types (19.5% vs 5.6% at 12 months, respectively) [10].

Despite these advances, optimal triage strategies for women infected with non-HPV16/18 types remain poorly defined, particularly in LMIC settings. Most trials have focused primarily on HPV16/18-positive women, leaving the substantial population of women with non-16/18 hrHPV infections comparatively understudied [11]. This knowledge gap is particularly critical in sub-Saharan Africa, where non-16/18 types account for a larger proportion of hrHPV infections [12] and associated lesions than in high-income settings [11]. Furthermore, although cytology-based triage remains the conventional approach, it demands a robust cytopathology infrastructure and technical expertise that are often limited in resource-constrained environments. The potential of alternative, risk-stratified triage models—incorporating factors such as age, HIV serostatus, smoking history, long-term oral contraceptive use, or multiple hrHPV-type co-infections—to improve diagnostic efficiency without sacrificing sensitivity has not been systematically evaluated in these settings.

Given the high burden of cervical precancerous lesions, the logistical limitations of cytology, and the evolving landscape of HPV-based screening, there is a compelling need to identify triage strategies that are both effective and contextually feasible. This proposed non-inferiority randomized controlled trial, titled “*Risk-Stratified versus Cytology-Based Triage of Non-HPV16/18-Positive Women* (*STRAT-CIN Trial*)”, is designed to address this evidence gap. The primary objective is to determine whether a risk-stratified triage algorithm is non-inferior to standard cytology-based triage in detecting high-grade cervical intraepithelial neoplasia (CIN2+) among women positive for non-HPV16/18 high-risk types. *The central hypothesis is that, among non-HPV16/18-positive women, the risk-stratified triage approach will achieve diagnostic sensitivity comparable to cytology while reducing unnecessary colposcopy referrals*. The secondary objectives are to (1) compare referral rates, colposcopic yield, and diagnostic performance metrics between the two triage strategies, and (2) identify key clinical and demographic predictors of CIN2 + among women infected with non-HPV16/18 hrHPV types.

## Methodology

### Study Design and Settings:

This study (*STRAT-CIN Trial*) proposes a two-arm, parallel, open-label, non-inferiority randomized controlled trial among sexually-active women at the Cytology and Colposcopy clinics of the Lagos University Teaching Hospital (LUTH), Nigeria, between June 2026 and January 2027. LUTH is the foremost healthcare institution in Lagos and serves as a referral centre for other government-owned and private hospitals in Lagos and its neighbouring states. The hospital provides a variety of care, including integrated gynecologic oncology prevention services such as Pap smearing, HPV testing and colposcopy services, including biopsy and histology. Laboratory analyses will be performed at the Department of Anatomic and Molecular Pathology (AMPATH), College of Medicine, University of Lagos, equipped with facilities for cytology, histopathology, and HPV genotyping [13].

### Participants:

The study population will consist of women aged 30–65 years who are hrHPV-positive for non-HPV16/18 types following primary HPV DNA testing during routine cervical cancer screening. Inclusion criteria will include laboratory confirmation of hrHPV infection with one or more non-HPV16/18 types (e.g., 31, 33, 35, 39, 45, 51, 52, 56, 58, 59, 66, or 68) using the validated Xpert^®^ HPV platform, age 30–65 years, and willingness to provide written informed consent and comply with study follow-up. Exclusion criteria will include the detection of HPV16 and/or HPV18 infection (triaged per standard-of-care protocols), previous diagnosis of CIN2+, cervical cancer, or history of hysterectomy, current pregnancy, immunosuppression unrelated to HIV, or prior HPV vaccination, and inability to provide informed consent or complete study procedures.

### Study endpoints:

The primary endpoint is the proportion of histologically confirmed CIN2 + lesions in each study arm, and the secondary endpoints are (1) diagnostic performance metrics (sensitivity, specificity, PPV, NPV) of the risk-stratified algorithm versus cytology for CIN2 + detection; (2) referral rates for colposcopy following triage in each arm; (3) colposcopic yield, defined as the proportion of referred women with histologically confirmed CIN2+; and (4) clinical and demographic predictors of CIN2+.

### Sample size calculation:

Sample size was calculated based on the primary objective of testing the non-inferiority of the risk-stratified algorithm compared with cytology-based triage for detecting CIN2+. Assuming a CIN2 + detection rate of 94% for cytology-based triage [14], a non-inferiority margin of 10%, a one-sided alpha of 5%, a power of 80%, and accounting for a 5% non-response or missing data rate, we estimate that n = 148 non-16/18 HPV-positive women (74 per arm) will be required to detect non-inferiority. This sample size will also provide > 80% power to detect a 20% relative reduction in unnecessary referrals (secondary endpoint) between study arms.

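### The 94% cytology rate behind n = 148 does not fit the primary endpoint, and at the protocol's own 5.6% the 10-point margin is larger than the control rate

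*Protocol article*

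**What the plan says.** The Sample size calculation section takes a "detection rate of 94% for cytology-based triage", a 10% margin, one-sided alpha of 5%, 80% power and 5% loss. It arrives at 148 non-16/18 HPV-positive women, 74 per arm.

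Under Study endpoints, "The primary endpoint is the proportion of histologically confirmed" CIN2+ in each arm. Sensitivity, with the other accuracy measures, and colposcopic yield are listed separately as secondary endpoints.

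The Statistical analysis plan section analyses the primary endpoint by intention to treat as a difference in proportions. Non-inferiority requires the lower limit of the 95% CI to lie above −10%.

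The Introduction cites an external trial for the CIN2+ risk with HPV16/18 against other high-risk types: "19.5% vs 5.6% at 12 months, respectively". It words the central hypothesis as a statement about sensitivity: the new triage "will achieve diagnostic sensitivity comparable to cytology while reducing unnecessary colposcopy referrals".

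Under Study procedures, only triage-positive women have colposcopy and biopsy. Triage-negative women are retested at 12 months.

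**The concern.** A rate of 94% in the control arm would mean that almost every randomised HPV-positive woman has confirmed CIN2+. That does not fit an arm made up of all non-16/18 HPV-positive women without a previous CIN2+ diagnosis, nor a cited risk of 5.6%. It looks like a rate with a different denominator: women who have CIN2+.

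If so, the planning rate and the hypothesis describe one quantity and the primary endpoint another. The stated power would then not describe the planned test. The margin is affected too: 10 points is a modest loss from 94%, but it is more than the whole of 5.6%.

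**Working it through.** **1. Reproducing the plan.** Inputs from the Sample size calculation: control rate 0.94, margin 0.10, one-sided alpha 0.05, power 0.80, loss 5%. The rate in the risk-stratified arm is not stated and is taken as equal.

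n per arm = (1.645 + 0.842)² × 2 × 0.94 × 0.06 / 0.10² = 69.7, so 70. Then 70 / 0.95 = 73.7, so 74 per arm and 148 in total. The match is exact, so 94% was used as the event proportion among randomised women.

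**2. The endpoint as defined, at 5.6%.**

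- Expected CIN2+: 74 × 0.056 = 4.1 per arm; 148 × 0.056 = 8.3 in total.
- 95% CI half-width for the difference: 1.96 × √(2 × 0.056 × 0.944 / 74) = 0.074, or 7.4 points.
- Same formula, same margin, one-sided 5%: (1.645 + 0.842)² × 2 × 0.056 × 0.944 / 0.10² = 65.4, so 66; with 5% loss 70 per arm, 140 in total.

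The totals are close because p(1 − p) is 0.0564 at 0.94 and 0.0529 at 0.056.

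**3. Sensitivity to the rate.** Power = Φ(0.10 / √(2p(1 − p)/70) − z), with z = 1.645 for one-sided 5% and 1.96 for the 95% CI rule. Rates other than 5.6% are assumptions, and these are normal approximations resting on few events.

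| CIN2+ rate, both arms | Expected CIN2+ per 74 women | Power, one-sided 5% | Power, 95% CI rule |
|---|---|---|---|
| 2% | 1.5 | over 99% | 99% |
| 5.6% | 4.1 | 82% | 73% |
| 10% | 7.4 | 63% | 50% |
| 20% | 14.8 | 43% | 32% |

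Power is highest where there are fewest cases, because there the margin dwarfs the rate.

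**4. What the margin allows at 5.6%.** A triage that detects no CIN2+ has a true difference of 0 − 5.6 = −5.6 points, inside −10. With 70 per arm and no cases in that arm:

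- Wald: 3 control cases give a lower limit of −(0.0429 + 1.96 × √(0.0429 × 0.9571 / 70)) = −0.090, which passes; 4 cases give −0.112, which fails. P(3 or fewer cases | 70, 0.056) = 0.44.
- Newcombe: 2 control cases give −0.098, which passes; 3 cases fail. P(2 or fewer cases) = 0.24.

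With 74 per arm the figures are 40% and 21%.

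**5. If 94% is meant as a sensitivity.** The 70 per arm must then be women with CIN2+. At 5.6% that is 70 / 0.056 = 1,250 HPV-positive women per arm. Even so, sensitivity would not be directly estimable, because triage-negative women have no immediate histology and the number of missed lesions is unknown.

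**The case against.** The strongest defence is numerical. At 5.6% with the stated margin and alpha, the same formula asks for 140 women and the plan has 148. A reader might infer that correcting the rate makes the trial far too small; the documents do not support that. Results such as about 1,059 evaluable women per arm follow only from a tighter margin (there 2.8 points, half of 5.6%, at one-sided 2.5%), which the protocol does not state. The fall from 82% to 73% comes from a separate mismatch, between the one-sided 5% used for sizing and the 95% CI used for the decision. What does not stand is the inference that the design is therefore sound: the agreement is accidental, disappears at 10% or 20%, and leaves the margin larger than the rate.

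Second, a reader might conclude that 94% must be a sensitivity. The article never says so and its cited source is not at hand. It is a reasonable inference from the size of the figure and the wording of the hypothesis, no more.

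Third, the endpoint wording could be stretched to mean the share of lesions that are detected. But sensitivity is a separate secondary endpoint, the analysis is by intention to treat, and the 74 per arm are HPV-positive women.

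Fourth, 5.6% is a 12-month risk from an external trial. It is neither a Lagos estimate nor a rate under cytology triage with biopsy of triage-positive women only. That stands, so about 4 cases per arm is conditional; over an assumed 2% to 20% the range is 1.5 to 15.

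Finally, a triage that finds nothing is a limiting case, not a forecast for this algorithm, which refers every woman with any listed risk factor. It shows what the test would tolerate.

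**Conclusion.** The point holds as an internal inconsistency, not as an arithmetic error. The 94% is not a plausible control-arm value of the primary endpoint at any rate considered here (2% to 20%), so the unqualified 80% power belongs to another quantity.

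The main consequence is not that 148 is numerically too small. It is that the primary conclusion would rest on about eight CIN2+ cases in all, with a CI half-width of about 7.4 points, judged against a margin wider than the control rate. This rests on 5.6% as the planning rate. At any control rate below 10%, a triage that finds nothing still lies inside the margin. At higher rates that problem recedes, but power falls to 63% or less at one-sided 5% and about 50% or less under the 95% CI rule.

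**What to change.** - **Rate.** In the Sample size calculation, replace 94% with the expected proportion of randomised women in whom cytology triage will detect CIN2+, with its source and a range.
- **Cases, precision, power.** Over that range, restate the expected number of cases, the CI half-width, and the power under the 95% CI rule of the Statistical analysis plan section, in place of the unqualified 80%.
- **Margin.** State that −10 points cannot exclude a triage that finds nothing when the rate is below 10%. Then either re-express the margin relative to the expected rate and restate the resulting power, or limit the primary conclusion to estimation with a CI.
- **Hypothesis and endpoint.** Make the Introduction's hypothesis and the primary endpoint refer to the same quantity. Which of them moves is the sponsor's choice; if sensitivity is chosen, its estimability has to be addressed.

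The cost is redrafting, and the Study Status section says that recruitment had not begun at submission. The estimation route needs no extra women but gives up the non-inferiority claim. A tighter margin could not be met with 148 women: purely as an illustration, 2.8 points at 5.6% needs 834 evaluable per arm at one-sided 5% (878 with 5% loss), or 1,059 at one-sided 2.5% (1,115 with loss).

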### Study procedures, randomization, and blinding:

The study investigators will screen and identify eligible non-HPV16/18-positive women for the study. Eligible women will be invited to participate in the study after receiving a comprehensive explanation of its purpose, procedures, potential risks and benefits, and will provide written informed consent before enrolment. Once consent is obtained, an interviewer-administered questionnaire will be applied to obtain baseline information on sociodemographic characteristics, reproductive and sexual history, and HIV and HPV status using the electronic case report form (eCRF) on the REDCap database hosted on a secure CMUL server with audit trails and user authentication. Eligible participants will then be randomized 1:1 using a computer-generated permuted block randomization sequence (block sizes of 4–6) stratified by age (< 35 vs ≥ 35 years) and HIV status [Figure 1]. Allocation concealment will be maintained using sequentially numbered, opaque, sealed envelopes prepared and safeguarded by an independent trial statistician.

**Intervention arm (risk-stratified triage)**: Participants will undergo triage using a risk-stratified algorithm incorporating a composite of readily available clinical and demographic data, including older age ≥ 35 years, HIV seropositivity with CD4 < 200 cells/mm^3^, cigarette smoking, long-term oral contraceptive use > 5 years, and multiple hrHPV genotype infections, to identify women at the highest risk of CIN2+ [15, 16]. Women with any of these risk factors will be referred for colposcopy, while those without will undergo repeat testing at 12 months.**Control arm (cytology-based triage)**: Participants will undergo reflex cytology (Pap test) interpreted per the Bethesda 2014 classification [17]. Women with atypical squamous cells of undetermined significance (ASC-US) or higher will be referred for colposcopy; those with normal cytology will undergo repeat testing at 12 months.

Colposcopy and biopsy will be performed for all screen-positive women in both arms. Histopathologic diagnosis (CIN1, CIN2, CIN3, or carcinoma) will be confirmed by two independent pathologists blinded to group allocation. Blinding of participants and clinicians is not feasible due to the procedural nature of triage methods; however, laboratory personnel and outcome assessors (cytologists, pathologists, and data analysts) will remain blinded to group allocation.

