### Statistical analysis plan:

All analyses will follow the intention-to-treat (ITT) approach, supplemented by per-protocol sensitivity analyses. Descriptive statistics will summarise participant characteristics. The primary endpoint (CIN2 + detection) will be compared between arms using the proportional difference with corresponding 95% confidence intervals (CI). Non-inferiority will be concluded if the lower bound of the 95% CI for the difference (risk-stratified – cytology) is above the pre-specified non-inferiority margin (–10%). Referral rates, colposcopic yield and diagnostic performance metrics will be compared using chi-square or Fisher’s exact tests. ROC curve analysis will assess the discriminative performance of the triage methods. Logistic regression will be used to identify independent predictors of CIN2+, adjusting for age, HIV status, parity, and other covariates. Missing data will be handled using multiple imputation, assuming data are missing at random [18]. All analyses will be conducted using Stata version 18 (StataCorp LLC, Texas, USA).

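### The trial is sized at one-sided 5% but judged on a 95% confidence interval, so power on its own assumptions is about 70%, not 80%

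*Protocol article*

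**What the plan says.** In the protocol article, *Sample size calculation* gives these planning inputs:

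- Control rate: "Assuming a CIN2 + detection rate of 94% for cytology-based triage".
- Margin, alpha and power: "a non-inferiority margin of 10%, a one-sided alpha of 5%, a power of 80" per cent.
- Loss: "accounting for a 5% non-response or missing data rate".
- Result: "n = 148 non-16/18 HPV-positive women (74 per arm) will be required to detect non-inferiority".

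*Statistical analysis plan* sets the success criterion: "Non-inferiority will be concluded if the lower bound of the 95% CI for the difference" (risk-stratified minus cytology) lies above −10%. The Methods paragraph of the abstract gives the same criterion. The document mentions neither a 90% interval nor a one-sided 95% bound, and nothing links the planning alpha to the interval level.

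**The concern.** The lower limit of a two-sided 95% interval is a one-sided 2.5% test, while the sample size section plans a one-sided 5% test. If 148 came from the 5% level, the quoted 80% power belongs to a rule the trial will not use, and the true power for the primary comparison is lower.

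The mismatch also leaves two significance levels on record for the only success criterion. If it is first noticed once data exist, moving between a 90% and a 95% interval becomes a post hoc choice, and near the margin that choice can decide the conclusion.

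**Working it through.** **Inputs.** From *Sample size calculation*: control rate 0.94, margin 0.10, one-sided alpha 0.05, power 0.80, loss 5%, 74 per arm. From *Study procedures, randomization, and blinding*: 1:1 allocation. From *Statistical analysis plan*: 95% interval, limit −10%. The detection rate expected in the risk-stratified arm is not stated. I take it as 0.94 (true difference zero), an assumption supported by the fact that it reproduces the plan's number.

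**Step 1: reproduce 148.** With the unpooled normal approximation,

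n per arm = (z₁₋α + z₀.₈₀)² × 2 × 0.94 × 0.06 / 0.10²

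where 2 × 0.94 × 0.06 = 0.1128.

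- One-sided 5%: (1.6449 + 0.8416)² × 0.1128 / 0.01 = 69.7, so 70. Then 70 / 0.95 = 73.7, so 74 per arm and **148** in total. This matches the plan exactly.
- One-sided 2.5%: (1.9600 + 0.8416)² × 0.1128 / 0.01 = 88.5, so 89. Then 89 / 0.95 = 93.7, so 94 per arm and **188** in total.

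The stated size therefore comes from the one-sided 5% level.

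**Step 2: power under each rule.**

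Power = Φ(0.10 / √(0.1128 / n) − z₁₋α)

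- n = 70: 0.10 / √(0.1128 / 70) = 2.491. With z = 1.645, Φ(0.846) = 80.1%. With z = 1.960, Φ(0.531) = **70.2%**.
- n = 74 (no loss): 0.10 / √(0.1128 / 74) = 2.561. With z = 1.645, Φ(0.916) = 82.0%. With z = 1.960, Φ(0.601) = **72.6%**.

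**Step 3: check by exact binomial enumeration**, 94% in both arms, success if the lower limit exceeds −10%:

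| Interval method | n = 70, 90% CI | n = 70, 95% CI | n = 74, 90% CI | n = 74, 95% CI |
|---|---|---|---|---|
| Wald | 78.8% | 71.5% | 82.1% | 75.7% |
| Newcombe | 74.2% | 62.4% | 76.4% | 63.0% |
| Score | 73.4% | 58.6% | 76.4% | 62.2% |

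No 95% column reaches 80%. The gap between the 90% and 95% columns is the effect of the alpha mismatch. The gap between rows is the effect of the interval method, which is a separate matter.

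**Step 4: can it change the conclusion?** Take 65/70 detected in the risk-stratified arm and 67/70 in the cytology arm. The difference is −2.86 points and the Wald standard error is √(0.9286 × 0.0714 / 70 + 0.9571 × 0.0429 / 70) = 0.0392.

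- 90% interval: −2.86 − 1.645 × 3.92 = −9.3 points, so non-inferior.
- 95% interval: −2.86 − 1.960 × 3.92 = −10.5 points, so not shown.

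**The case against.** The strongest reply is that the stated rule is the stricter one. It appears identically in two places, does not raise the chance of falsely declaring non-inferiority, and using a 90% interval later would be a visible departure from it. This is right about type I error, and it tempers the worry about a post hoc choice. It does not make the stated 80% power true.

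Second, the text never writes "two-sided". If a one-sided 95% bound was meant, planning and analysis agree. That is the less natural reading of a lower bound of a 95% confidence interval, and a reader cannot tell that it was intended, so the wording would need correcting in that case too.

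Third, the lower exact figures (59% to 63% with Newcombe or score intervals) should not be charged wholly to the alpha mismatch. With a 90% interval those methods already give only 73% to 76%. At 70 per arm the mismatch itself accounts for about 12 points (74.2 − 62.4, Newcombe) to 15 points (73.4 − 58.6, score). This stands: the protocol names no interval method, and that choice can be left to the analysis plan. The like-for-like figure is 70.2%, from the approximation that produced 148. For the same reason, 89 evaluable per arm gives 80% under the normal approximation (80.2%) and exact Wald (80.5%), but only 74.5% with Newcombe and 71.5% with score intervals.

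**Conclusion.** The concern holds. The sample size and the decision rule use different significance levels. On the plan's own assumptions, power for the rule as written is about 70% (70.2% with 70 evaluable per arm, 72.6% with all 74), against 80% claimed. The chance of missing true non-inferiority rises from about 20% to about 30%.

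This rests on three assumptions: equal 94% detection in both arms, the ordinary two-sided meaning of a 95% interval, and the normal approximation behind the plan's own number. Whether 94% is a sensible planning rate for this endpoint is a separate question. The mismatch would remain at any other rate, though its size in power would change. Because it affects the primary test and its only success criterion, it should be corrected before the first woman is enrolled.

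**What to change.** Use one level throughout.

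- **Preferred:** keep the 95% interval rule in the abstract and *Statistical analysis plan*, and say that it is two-sided. In *Sample size calculation*, replace the one-sided 5% alpha with one-sided 2.5%, state the detection rate assumed in the risk-stratified arm, and restate power as about 70% for 148 women. For scale, 80% power at this level would take 89 evaluable and 94 randomised per arm, 188 in total, by the same approximation.
- **If one-sided 5% is truly intended:** change the decision rule to the lower limit of the two-sided 90% interval in both the abstract and *Statistical analysis plan*, before enrolment. The 148 and the 80% (80.1% at 70 per arm) then stand under the normal approximation.

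If the 94% planning rate is revised, make both changes together, because the 70% and the 188 both depend on it.

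The cost is a sentence or two in the protocol, plus the registry entry if it carries the same figures. *Study Status* says recruitment has not begun, so the change can be made without any knowledge of the data. Under the preferred option the price is a less favourable power statement.

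### The claimed power of more than 80% for a 20% relative reduction in unnecessary referrals needs a control rate of about 90%; at control rates of 30–70% the power is 12–42% (two-sided 5%)

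*Protocol article*

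**What the plan says.** The trial is sized on the non-inferiority endpoint: "n = 148 non-16/18 HPV-positive women (74 per arm) will be required to detect non-inferiority", after "accounting for a 5% non-response or missing data rate" (Sample size calculation). The same section then adds: "This sample size will also provide > 80% power to detect a 20% relative reduction in unnecessary referrals (secondary endpoint) between study arms".

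No control rate, denominator, alpha or sidedness is attached to that second statement. The article gives these related details elsewhere:

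- Study endpoints lists "referral rates for colposcopy following triage in each arm" and, separately, colposcopic yield among referred women. It does not list unnecessary referrals under that name.
- Statistical analysis plan: "Referral rates, colposcopic yield and diagnostic performance metrics will be compared using chi-square or Fisher’s exact tests".
- Abstract, Methods: "statistical significance will be set at P < 0.05", with no sidedness given.

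**The concern.** A relative reduction of 20% is a small absolute difference unless the control rate is high: 6 percentage points at 30%, 10 at 50%, 14 at 70%. About 70 women per arm is few for differences of that size, so an unconditional claim of more than 80% power looked doubtful.

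Fewer unnecessary referrals is half of the trial's central hypothesis (Introduction) and one of the benefits named in the Discussion. A reader who trusts the stated power would take a non-significant referral comparison as evidence that the two strategies refer alike, when the test had little chance of showing the difference.

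**Working it through.** **Inputs from the protocol article.** 74 women per arm, 1:1 allocation; 5% loss, so about 70 evaluable (74 × 0.95 = 70.3); effect p₂ = 0.8 × p₁; chi-square or Fisher's exact test; significance at 0.05, taken as two-sided. The control rate p₁ is not given and is varied as an assumption.

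**The plan's own primary figure first.** With 94% in both arms, a margin of 0.10, one-sided 5% and 80% power:

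n = (1.645 + 0.842)² × 2 × 0.94 × 0.06 / 0.10² = 69.7, so 70 per arm. Then 70 / 0.95 = 73.7, so 74 per arm and 148 in total. This reproduces exactly.

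**Power for the referral comparison.** With p̄ = (p₁ + p₂)/2,

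power = Φ{ [ (p₁ − p₂) − z·√(2p̄(1 − p̄)/n) ] / √([p₁(1 − p₁) + p₂(1 − p₂)]/n) }

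Example, p₁ = 0.50, p₂ = 0.40, n = 70, z = 1.960: the null standard error is √(2 × 0.45 × 0.55/70) = 0.0841 and the alternative standard error is √((0.25 + 0.24)/70) = 0.0837. Power = Φ[(0.100 − 1.960 × 0.0841)/0.0837] = Φ(−0.775) = 0.219.

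| Control rate | 70/arm, two-sided | 74/arm, two-sided | 70/arm, one-sided | 74/arm, one-sided |
|---|---|---|---|---|
| 30% | 12.2% | 12.7% | 19.8% | 20.5% |
| 50% | 21.9% | 22.9% | 32.3% | 33.6% |
| 70% | 40.2% | 42.1% | 52.8% | 54.8% |
| 80% | 56.0% | 58.4% | 68.1% | 70.2% |
| 90% | 78.1% | 80.3% | 86.4% | 88.1% |
| Control rate at which power is 80% | 90.8% | 89.9% | 86.6% | 85.5% |

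Exact enumeration of the two-sided chi-square test agrees closely (for example 12.5%, 22.2% and 40.1% at 30, 50 and 70% with 70 per arm). Fisher's exact test, which the plan also allows, does worse: 9–36% at control rates of 30–70%, and 73–75% even at 90%.

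**What the claim would need.** For 80% power at two-sided 5%, the number per arm is 859 at a control rate of 30%, 388 at 50%, 186 at 70% and 74 at 90%. Conversely, with 70 per arm the intervention rate must fall from 50% to 27.1% (a relative reduction of about 46%) or from 30% to 11.0% (about 63%).

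**Other readings.**

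- *20 percentage points absolute* (not what is written): two-sided power is 66–87% over control rates of 30–90%, above 80% only towards the ends of that range.
- *Referred women as the denominator*: assume 22 control and 37 intervention referrals (30% and 50% of 74), or 37 and 64 (50% and 86%). For unnecessary shares of 80–94%, two-sided power is 24–44% and 39–69% respectively. At one-sided 5% the most favourable corner (37 and 64 referred, 94% share) gives 81%.

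**The case against.** The strongest reply is that the denominator may be referred women. A share near or above 90% is then quite plausible: the Introduction cites a 12-month CIN2+ risk of 5.6% for non-16/18 types, which leaves 94.4% without CIN2+ before any enrichment by triage. A control rate of 94.4% with 70 to 74 per arm would give about 89–90% power two-sided, and this may be where the sentence came from. But that calculation counts every randomised woman as referred. With only the referred women in the test, 80% is reached only when referral is very high (60 referred per arm, 81% of 74, gives 83% at a 94.4% share) or at the one-sided corner shown above.

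Two further points stand as limits. The only alpha in the Sample size calculation section is one-sided 5%; if it was meant here, power at 30–70% is 20–55% rather than 12–42%. And the 30–70% range is an assumption, because the article gives no rate.

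It is also fair that the complement of colposcopic yield is the share of referred women without CIN2+, so the quantity is not wholly absent from the endpoints; the label is loose rather than unrelated. The missing inputs could sit in a fuller document and are not the complaint. The complaint is a definite figure that only an extreme input makes true.

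**Conclusion.** The statement is wrong as written. With randomised women as the denominator, the design has more than 80% power for a 20% relative reduction only if about 90% or more of control women are referred without CIN2+ (two-sided 5%), or about 86% or more (one-sided 5%). Control women with normal cytology are not referred, so a 90% rate would leave at most 10% with a normal smear and cytology with almost no triage function. At control rates of 30–70%, which are assumed, two-sided power is 12–42%. With referred women as the denominator it is 24–69% on the assumed counts.

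The primary sample size reproduces and does not depend on this sentence. What is affected is how the referral comparison may be interpreted.

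**What to change.** Either delete the sentence, or replace it with the power actually available and the conditions it rests on:

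- Define an unnecessary referral, for example as referral without histologically confirmed CIN2+, with all randomised women as the denominator, and name it under Study endpoints.
- State the expected control rate with its source, the alpha and the sidedness. If no source exists, give a range and label it an assumption.

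Possible wording: *With 70 evaluable women per arm and a two-sided 5% test, power for a 20% relative reduction in the proportion of randomised women referred without CIN2+ is about 12%, 22% and 40% for assumed control proportions of 30%, 50% and 70%. The relative reduction detectable with 80% power is about 46% at a control proportion of 50% and about 63% at 30%.*

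The cost is one sentence and a less favourable figure. No change to the sample size follows unless the sponsor wants the referral comparison to be adequately powered. Recruitment had not begun when the article was submitted (Study Status), so the correction can be made before enrolment.
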